### **Interventions: Usual Care vs. Electronically Enabled Discharge Medication Reconciliation**

---

**Usual Care:** The community drug list is generally documented at the time of admission. For patients admitted through the emergency department, the triage nurse and ED pharmacist (weekdays only) are responsible for documenting the community medication list in the chart. This may be reviewed and updated by the admitting physician, resident, and/or nurse. When the patient is admitted directly to the unit, the admitting nurse and staff physician/resident are responsible for documenting the medication history. In

addition, there are 14 FTE pharmacists available on weekdays to provide inpatient clinical pharmacy service support for the medical and surgical units, including intensive care. Unit-based pharmacists may provide assistance in obtaining the community drug history, particularly for more complex medication regimens.

At discharge, the attending physician/resident uses the list of current hospital medication, with or without the community drug list (when available), to prescribe the discharge medication. Similar to other Canadian hospitals, the MUHC has implemented an electronic health record (OACIS), that integrates all relevant clinical information from hospital pharmacy, labs, diagnostic imaging, consult reports to be viewed by the treatment team (appendix 2). Active hospital medications can be viewed by accessing the patient's electronic OACIS record, the medication administration chart, or nurse's kardex. The patient is provided with a written discharge prescription to fill at community pharmacy, and may or may not receive verbal or written instructions about new medications or community medications that are being stopped or changed. If the community pharmacist has questions about whether they should continue pre-existing medications that are not included in the discharge medication, they ask the patient, and may call the physician or discharging unit of the hospital.

**Electronically enabled Discharge Reconciliation and Communication:** The experimental intervention has three components. *First*, at admission, the *community drug list* will be electronically retrieved from the RAMQ using the MOXXI real-time interface, and transferred to the hospital pharmacy system (Figure 4).. In a prior validation study, we have shown that RAMQ prescription claims achieve an accuracy of 100% for the drug dispensed, and 98.5% for the date of dispensing. We will include all drugs where the patient has an active supply of medication in the 7 days prior to admission, as well as provide the treatment team with the option of reviewing all drugs dispensed in the past 6 months using the MOXXI drug profile. The admitting team and hospital pharmacist will verify the list with the patient, add any other medications including over-the-counter

[figure not shown]

Figure 4 MOXXI Drug Profile: Medication Active Today (Vertical line) and Medication History (6 Months)

and herbal products, and the resulting list will be used to pre-populate the discharge module (Figure 5).

Second, at discharge, the attending physician/resident will write the discharge prescription using the *discharge reconciliation module*.

Figure 5 Discharge reconciliation and prescription module

The discharge reconciliation module will be integrated, and directly accessible through the patient's electronic OACIS record. It will display the current active hospital medications, and the verified community-based drug list, sorted by therapeutic class (e.g. antihypertensives, antidepressants) to facilitate reconciliation (Figure 5). The attending physician/resident will "click" on each of the hospital medications that should be included in the discharge prescription, and add any medications from the community drug list that should be continued. All community-based medications that are not included in the

discharge prescription will be automatically transferred to the discontinuation section. To assist in viewing the reconciliation process, dose changes will be separated from discontinued medication.

Third, the *discharge communication module* (Figure 6) will facilitate the identification and transfer of information on discontinued and changed medication to the respective dispensing pharmacy (ies) and prescribing physician(s) along with the reasons for these changes. The attending physician/resident will document *the reason for discontinuing or changing the dose of each medication* using a drop-down menu, an approach that has been validated by our group in prior research. A comment field is also available where additional information can be added using free text. The list of prescribed and discontinued medications will be printed, signed by the attending physician/resident, and a copy printed and retained for the chart.

Figure 6 Discharge Communication Module

For each discontinued medication or dose change, the dispensing pharmacy and prescribing physician will be identified from the community-based pharmacy claim record. The identity of the prescribing physician and pharmacy must be completed accurately for the pharmacy to receive payment from the RAMQ. Access to this information has been approved for this study by the provincial privacy commission (appendix 3). For each discontinued drug, the name of the patient, drug, and the reason for discontinuation, attending physician, hospital, and discharge date will be faxed to the respective dispensing pharmacy and prescribing physician. Fax numbers for prescribing

physicians will be retrieved from the Collège des médecins du Québec who will provide the research team with a monthly updated file of all licensed physicians in Quebec, their telephone and fax numbers. Fax numbers for community pharmacies will be retrieved from Vigilance, a pharmacy software provider that receives a monthly update of this information from the Association Québécoise des Pharmaciens Propriétaires, that is used by pharmacies to fax transferred prescriptions from one pharmacy to another. To

minimize the risk of transmitting confidential information to incorrect fax numbers, we will call the pharmacy and physician's office before faxing patient information to verify the fax number.

**Adherence to the Intervention:** Our main challenge will be to ensure that attending physicians/residents have sufficient training, motivation, and support to use the medication reconciliation module for the discharge prescription. The four conditions needed for successful adoption will be incorporated into the implementation of discharge reconciliation. First, we will train local leadership within each unit to champion the discharge reconciliation process comprising the unit service chief, head nurse, and liaison pharmacist. Second, we will pre-test and calibrate the user interface to minimize workflow disruption and maximize efficiency gains. Based on our experience of instituting electronic prescribing in the primary care setting, we expect that we can save 3 or more minutes per discharge prescription, by allowing relevant hospital and community-based prescriptions to be copied to the discharge prescription. Third, we will prepare, with the clinical champions, a blitz launch in each unit that will feature on-site support for completing the discharge prescription in each unit for the first 2 weeks. We have successfully used nursing and medical students, who are typically adept computer users, to provide real-time coaching and support for using new clinical computer applications. Last, we will monitor adoption by using application audit trails, and use this information to identify and remedy problems that may exist on certain units.

**Bias Control** The main challenge in *bias control* is the inability to blind staff to treatment assignment, and potential co-intervention. To control bias, the research assistant, expert panel, and analyst assessing the outcome of treatment will be blinded to unit and treatment allocation status. To assess bias related to possible co-interventions, the project coordinator will conduct a monthly review with the unit directors and hospital pharmacy to assess co-interventions (new initiatives that may modify the study outcomes), and we will use sensitivity analysis to assess the potential impact on the study outcomes. As the involvement of the hospital pharmacist in the patient's care likely reduces the risk of adverse events (e.g. through medication review), we will retrieve this information from the chart and assess whether hospital pharmacist intervention (yes vs. no) is a confounder by including this information as a patient-level variable in the analysis. In addition, as cluster randomization may not produce patients groups who have an equivalent risk of adverse events post-discharge (i.e. because randomization is by unit rather than by patient), we will assess whether patients admitted to the usual care vs. e-discharge units had a similar rate of hospitalizations, and ER visits in the 12 months prior to admission using RAMQ medical service data retrieved for each patient, and include prior ER/hospitalization history in the analysis to determine if it confounds the estimated effect of the intervention.

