An intention to treat approach will be used to analyze study results. To determine whether discharge reconciliation reduces the risk of adverse drug events post-discharge, we will use logistic regression within a generalized estimating equation framework to account for clustering of patients within unit. The presence of a probable or definite adverse event (yes vs. no) will be the outcome variable, hospital unit will be the defined clustering factor, and an exchangeable correlation matrix will be used to account for clustering of patients within unit. Discharge reconciliation will be fit as a dummy variable, using usual care as the reference group. We will use the same approach to assess the secondary outcome, ER visits and/or hospital re-admission. For both the primary and secondary outcome, we will assess, whether adjustment for co-interventions and baseline differences between patients in the usual care and intervention arm confound the effect of the intervention. In secondary analysis, we will assess whether the effect of the intervention is modified by hospital unit type (medicine vs. surgery vs. psychiatric), and patient characteristics that are associated with a higher risk of adverse events (age, number of medications at discharge) by including respective interaction terms in the logistic model and testing their significance using the Wald chi-square statistic.

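### Hospital pharmacist contact is to be tested as a confounder, although it arises after allocation and is partly a step of the intervention itself

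*Protocol*

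**What the plan says.** Four parts of the protocol bear on this.

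- **Bias Control.** The protocol expects that "the involvement of the hospital pharmacist in the patient's care likely reduces the risk of adverse events". Chart data on such involvement will therefore be collected, the plan being to "assess whether hospital pharmacist intervention (yes vs. no) is a confounder by including this information as a patient-level variable in the analysis".
- **Electronically enabled Discharge Reconciliation and Communication.** In the first component of the experimental intervention, "The admitting team and hospital pharmacist will verify the list with the patient". The verified list then fills the discharge module. Under Adherence to the Intervention, the local leadership trained to champion the process is described as "comprising the unit service chief, head nurse, and liaison pharmacist".
- **Usual Care.** Here the pharmacist's part is optional and selective: "Unit-based pharmacists may provide assistance in obtaining the community drug history, particularly for more complex medication regimens".
- **Data Management and Analysis.** The main analysis is by intention to treat, using a logistic model with generalised estimating equations: "Discharge reconciliation will be fit as a dummy variable, using usual care as the reference group". No pharmacist term is named. For both the primary and the secondary outcome the section then adds: "we will assess, whether adjustment for co-interventions and baseline differences between patients" in the two arms alters the intervention effect.

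No section separates pharmacist work that the intervention requires from pharmacist care given independently of it.

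**The concern.** A confounder must not be a consequence of the treatment. Chart-recorded pharmacist contact during the index stay comes after the unit has been allocated. On intervention units the protocol itself calls for part of it. By the protocol's own premise it also lowers the outcome risk. That is the description of a mediator. In usual care the same yes/no variable also marks patients with complex regimens, who may be at higher risk.

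Two things could go wrong. Adjusting for contact can remove the part of the benefit that works through the pharmacist, and it can set unlike patients side by side within the contact and no-contact groups. A change in the estimate after adjustment could then be taken as evidence of confounding when it is nothing of the kind.

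The path is not a minor one in the protocol's own account. The background credits pharmacist histories with reducing errors from 323 to 86 per 1,000 orders, against 157 for nurse-taken histories. It attributes 72% of discharge reconciliation errors to an incomplete pre-admission list.

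**Working it through.** The protocol states no figure for this point, so there is none to reproduce. The check has two parts.

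**1. Order and direction of the links**

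- Allocation precedes the covariate: units are randomised (Randomization), and contact is read from the chart of the later stay (Bias Control).
- Allocation may change the covariate: list verification is specified on intervention units and is optional in usual care.
- The covariate affects the outcome: stated under Bias Control.
- Patient risk may affect the covariate: usual-care help is directed at complex regimens.

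The first three links make contact a possible mediator. The fourth makes it a possible marker of patient risk, and more so in one arm than in the other.

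**2. Illustration of size**

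Inputs from the Sample size paragraph: control risk 15%, absolute reduction 5 points, hence 10%. The total odds ratio is (0.10/0.90) / (0.15/0.85) = 0.1111/0.1765 = 0.63.

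Assumed, because the protocol gives neither: the share of patients with contact in each arm, and the relative risk of an adverse drug event with contact (0.8, 0.7 or 0.5).

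One case by hand: contact 30% in usual care and 90% in the intervention arm, relative risk 0.7, contact unrelated to patient risk.

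- Usual care, no contact: 0.15 / (0.7 + 0.3 × 0.7) = 0.15/0.91 = 16.5%. With contact: 0.7 × 16.5% = 11.5%.
- Intervention, no contact: 0.10 / (0.1 + 0.9 × 0.7) = 0.10/0.73 = 13.7%. With contact: 0.7 × 13.7% = 9.6%.
- Odds ratio without contact: (0.137/0.863) / (0.165/0.835) = 0.80. With contact: (0.0959/0.9041) / (0.1154/0.8846) = 0.81.

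The adjusted odds ratio is therefore about 0.81, against a total effect of 0.63.

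The table gives the treatment odds ratio from logistic models that include the contact term. The models were fitted to expected counts without clustering, and every row is calibrated to 15% versus 10%. In the selective rows, half the patients have three times the risk of the rest. Usual-care contact is 15 points above its average in the high-risk half and 15 points below in the other half. Intervention-arm contact is unrelated to risk.

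| Contact, usual care → intervention | RR 0.8 | RR 0.7 | RR 0.5 |
|---|---|---|---|
| 30% → 30%, unrelated to risk | 0.629 | 0.629 | 0.627 |
| 30% → 60%, unrelated | 0.679 | 0.708 | 0.783 |
| 30% → 90%, unrelated | 0.737 | 0.810 | 1.035 |
| 50% → 90%, unrelated | 0.701 | 0.750 | 0.897 |
| 50% → 30%, unrelated | 0.598 | 0.581 | 0.540 |
| 30% → 60%, selective in usual care | 0.637 | 0.667 | 0.745 |
| 30% → 90%, selective in usual care | 0.614 | 0.679 | 0.882 |

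The total effect is the same in every row, so all movement away from 0.63 is produced by the adjustment. With equal contact there is essentially none. With unequal contact it can go towards or away from the null.

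**The case against.** The strongest reply is that the main result is safe, and that reply stands. A reader might infer that the primary estimate is itself biased. The documents do not support this: the intention-to-treat model is described with the treatment term alone, and the pharmacist variable enters only when confounding is assessed. Nor does the protocol state any rule by which an adjusted estimate would replace the unadjusted one. Equally, it does not say which leads if they differ.

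Other stronger readings also go too far.

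- *Every intervention patient has pharmacist contact.* This is not established. Verification is shared with the admitting team. The inpatient service is 14 full-time-equivalent pharmacists on weekdays, described for medical and surgical units. The argument needs only a difference between arms, and whether there is one is unknown.
- *Contact could never be a confounder here.* This is too absolute. With 28 units, 2 of them psychiatric, pharmacist coverage that existed before the trial could be unbalanced by chance. That is a legitimate worry, but a patient-level variable recorded after allocation is the wrong instrument for it.
- *The variable is purely the intervention step.* Bias Control gives medication review as its example, so it may partly capture independent care. As a plain yes/no it does not exclude intervention-required verification, and even independent review comes after allocation and may follow patient complexity.
- *All co-interventions share the fault.* They do not. The protocol defines them as new initiatives that might affect outcomes and assigns them to sensitivity analysis, which is reasonable where they are unrelated to allocation.

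It may also be said that the choice of leading estimate belongs in a statistical analysis plan. That is fair for the detail, but the protocol itself already names this variable as a candidate confounder.

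**Conclusion.** The point holds in a limited form. Patient-level pharmacist contact should not be assessed as a confounder, because it follows allocation, is partly prescribed by the intervention and is selective in usual care. If allocation changes recorded contact, the estimate adjusted for it is not the intention-to-treat effect, and a shift on adding it cannot be read as confounding.

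The size and direction are unknown. The range of about 0.61 to 1.04 around a total odds ratio of 0.63, when contact rises from 30% to 60-90%, rests wholly on assumed contact rates and pharmacist effects and ignores clustering. It shows what could happen and is not a forecast. If contact is equal between arms the matter has no practical effect. The planned adjustment for emergency visits and hospitalisations in the 12 months before admission is not in question, since these are fixed before admission.

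**What to change.** Amend Bias Control and Data Management and Analysis as follows.

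1. Remove patient-level hospital pharmacist contact from the variables assessed or adjusted for as confounders, for both outcomes.
2. State that the intention-to-treat estimate without that term is the leading result.
3. Restrict confounder adjustment to variables fixed before admission or randomisation: for example unit type, age, prior emergency visits and hospitalisations, and comorbidity. If chance imbalance in pharmacist service is the worry, use each unit's pharmacist coverage measured before the trial.
4. Report pharmacist contact by arm as a process measure, or use it in a mediation analysis labelled as such. If feasible, record list verification required by the intervention separately from other pharmacist care.
5. Keep co-interventions unrelated to allocation in the sensitivity analysis already planned. Do not treat as confounders those that could respond to allocation.

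The cost is a change of wording. The chart data are already to be collected. Only the pre-trial coverage measure and the split in item 4, if adopted, would add a little data work.

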## Outcome Assessment

**Adverse Drug Events:** Adverse drug events are defined as the occurrence of new signs and symptoms post-discharge that are judged to have a moderate to high probability of being drug-related. Adverse drug events will be assessed by: a) collecting self-reported patient information 30 days post-discharge, b) retrieving chart and administrative data on drugs that were started, stopped or continued at discharge as well as acute and chronic health problems, and c) reviewing and adjudicating the presence of an adverse event and the probability of it being drug related by a blinded expert panel review of each patient's chart and post-discharge interview data using the Naranjo criteria.

1) *Self-Report Interview:* Patient self-report will be used because it is the most sensitive method of adverse drug event detection, identifying an additional 28% of adverse events compared to medical chart review, of which 13% are considered serious. A modification of the Australian two-step adverse reaction and drug event report will be employed to solicit patient feedback on potential adverse events, and their characteristics. Both questionnaire and telephone interview versions of this protocol have been assessed. As the telephone version provides higher sensitivity of event detection, we have elected to use the latter. In the first step, patients will be asked to report any new health problem or change in their condition since discharge that they think may be related to their medication(s). In the second step, a review of systems is

conducted using directed probes for changes in systems-related symptoms or signs that may be drug-related (e.g. skin rash, cough). For positive responses, patients will be asked to describe each new problem, and indicate when it started in relation to the initiation of drug treatment post-discharge.

Most adverse events occur early in the post-discharge period, therefore, we will conduct the follow-up interview in the first 25 to 30 days post-discharge. A trained research assistant will conduct patient follow-up interviews, **blinded** to intervention status. Five attempts will be made to contact the patient. If a patient cannot be reached successfully, we will send a questionnaire version of the adverse reaction and event report by mail, with an accompanying letter from their attending physician, and self-addressed stamped envelope for return. We will assess the quality of the interview and documentation provided by the research assistant by a monthly quality control check using standardized patient interviews. These quality control methods, that have been employed by our team in past research, will allow us to estimate the agreement between actual documentation and expected documentation, where the standardized case represents the gold standard. Additional training will be employed as needed to correct deviations from the protocol. Patient interview data will be entered into an ACCESS database.

*Chart Abstraction:* For each patient, a trained nurse abstractor, blinded to intervention status, will abstract the medical chart. We will abstract dates of admission and discharge, admitting and discharge unit, patient demographics, health problems at admission and discharge, major procedures (surgeries, treatment interventions), and medications at admission, during the hospital stay and at discharge, including medications that were stopped and changed by the in-hospital treatment team. Health problems will be coded using ICD10, medications by generic chemical code using Anatomic-Therapeutic Classification system, and procedures by Canadian Classification and Diagnostic and Therapeutic Procedures (CCP). Data will be entered using the MOXXI chart abstraction system as it permits text entries (e.g. hydrochlorithiazide 10mg, rheumatoid arthritis) to be mapped to the respective classification system and stored by patient identifier in the MOXXI Oracle database. A case summary record, that includes the community drug list, hospital drug list, discharge abstract, discharge medications and patient self-report, will be prepared for causality assessment by the expert panel.

*Expert Review and ADE Assessment:* A number of methods have been developed for expert panels to assess probability that a given event is drug-related on the basis of patient data. None of the scoring systems are accepted as a gold standard, but the Naranjo criteria for ADE assessment is the most widely used method of ADE causality assessment in practice. The Naranjo instrument uses patient self-report or chart review data to assess the presence or absence of ten criteria related to the adverse event (e.g. renal failure). The relative importance of each criterion is weighted from -1 to +2. The sum of criteria-specific weights is used to classify the probability that the event was drug-related into one of 4 categories: definite, probable, possible or doubtful. Inter-rater agreement in assessing events using Naranjo criteria is good to excellent (kappa: 0.69-0.86) and intra-rater agreement varies between kappa=0.64-0.95. Naranjo scored events correlate with other similar measures such as the Kramer ADE probability assessment instrument ( $r = 0.82$ ). Gold standard ADEs will be defined as those with a causality assessment score classified as definite or probable. Three clinicians who are part of the study team will assess the Naranjo criteria. Each clinician will receive the patient self-report for all patients with a positive response to the open-ended query of about adverse effects, or system-specific probes, as well as all clinical information retrieved from the chart. Clinicians will be **blinded** to the patient's intervention status (usual care vs. discharge reconciliation). Each clinician will independently score each patient on the 10 Naranjocriteria. Each clinician's score will be used to classify that patient as having a definite (score $\geq 9$ ), probable (score 5-8), possible (score 1-4) or doubtful (score=0) adverse drug event. All patient cases where there is a difference in final classification will be reviewed and discussed by the panel of three clinicians to reach a consensus classification. We will test inter-rater agreement using 10 training charts before the start of the study, and each month during follow-up using one standardized chart per month. Agreement in scoring on the training and monthly quality control charts will be assessed by an intra-class correlation and in the Naranjo classification by weighted kappa.

*ER Visit/Hospital re-admission:* All visits to the emergency room and/or hospital re-admission in the 30 days post-discharge will be measured using the RAMQ provincial health care databases. This approach ensures that all ER visits and re-admissions are included, not just those occurring to at the MUHC. This is

important because ambulances will transport individuals to the closest, open emergency room/hospital which often is not the discharging institution. Almost all hospital-based physicians in Quebec are remunerated on a fee-for-service basis, and for each medical service delivered, physicians are required to accurately record the treating establishment, and the location of the service (e.g. ICU, ER, day hospital, inpatient unit), because location and type of establishment determine the level of remuneration. For each consenting patient, the RAMQ will retrieve all records of services provided in the month after discharge. Patients will be classified as having an ER visit if they have a record of service with a location of a hospital emergency room, and a re-admission if they have a service delivered from an in-patient general hospital unit. In secondary analysis, we will retrieve all ICD10 diagnostic codes recorded for ER visits and re-admissions to provide descriptive information on potential reasons for the visit/re-admission.

